## Abstract

**Background:**

Pregnant women living with HIV (WLH) face daily challenges maintaining their own and their babies' health and mental health. Standard Prevention of Maternal to Child Transmission (PMTCT) programs are not designed to address these challenges.

**Methods/Design:**

As part of a cluster randomized controlled trial, WLH are invited to attend four antenatal and four postnatal small group sessions led by a peer WLH (a Peer Mentor). The WLH and their babies are assessed during pregnancy and at one week, six months, and twelve months post-birth. Mobile phones are used to collect routine information, complete questionnaires and remain in contact with participants over time. Pregnant WLH (N = 1200) are randomly assigned by clinic (N = 8 clinics) to an intervention program, called *Masihambisane *(n = 4 clinics, n = 600 WLH) or a standard care PMTCT control condition (n = 4 clinics; n = 600 WLH).

**Discussion:**

Data collection with cellular phones are innovative and effective in low-resource settings. Standard PMTCT programs are not designed to address the daily challenges faced by WLH; Peer Mentors may be useful in supporting WLH to cope with these challenges.

**Trial registration:**

ClinicalTrials.gov registration # NCT00972699

## Background

An estimated 1.4 million pregnant women are women living with HIV (WLH) in low and middle income countries (LMIC) [1]. South Africa has the highest total number of people living with HIV (5.7 million), of whom 3.2 million are women [1] and more than 200,000 are pregnant WLH in need of antiretrovirals [2]. The national HIV prevalence has stabilised around 11% [3], with the highest rates in the Kwa-Zulu-Natal and Gauteng Provinces. Up to 40-60% of pregnant women in Kwa-Zulu-Natal are HIV positive [4]. Antiretroviral (ARV) medications can reduce HIV transmission to less than 2% at childbirth and exclusive breastfeeding for six months also minimizes risk of transmission [5]. Therefore, effective programs to prevent mother-to-child transmission (PMTCT) for WLH in South Africa are urgently needed.

The goal of this cluster randomized controlled trial (RCT) is to evaluate a clinic-based strategy for increasing uptake of PMTCT and to improve maternal health behaviors over time. The *Masihambisane *program is leveraging the unique intervention opportunities created by pregnancy. Pregnancy requires mothers to adopt new routines and behaviors. HIV, alcohol and nutrition are linked to daily behaviors and habits, which are significantly easier to shift during life transitions compared to periods of stable living [6]. The birth of a child is a major life transition as relationships become reordered and there are changes in sleeping, eating, socializing, and working patterns. This creates the opportunity for "upstream" programming of new attitudes and behaviours [6].

WLH's experience of HIV-related stigma is often associated with poor antenatal and postnatal adherence to HIV-related regimens and healthy lifestyles [7,8]. Having a peer for support at the time of diagnoses who also introduces and supports health regimens (e.g., ARV medication adherence, exclusive breastfeeding) can be emotionally powerful [9]. There is a history of peer self-help interventions in LMIC that utilize peer advocates, including Alcoholics Anonymous [10], Widow-to-Widow [11], and community popular opinion leaders [12]. The mothers2mothers programme (m2m) is an HIV perinatal support program that initiated placing WLH as Peer Mentors in clinics beginning in 1990 http://www.m2m.org. The Masihambisane Project builds on the m2m programme by systematically training the Peer Mentor WLH to support PMTCT goals.

PMTCT programs typically focus on three biomedical interventions: maternal HIV testing; ARV provision in preparation for and during childbirth; and infant ARV medication adherence for six weeks until infant serostatus is established by PCR testing [5]. While ARV treatment is highly effective, only 21% of pregnant women in LMIC were tested for HIV in 2008, and fewer than half of those testing seropositive received ARV medication [1]. Beginning in 2001 [13], routine PMTCT has been available in South Africa. By 2007/08, 81% of pregnant women attending public antenatal clinics in South Africa had been tested. However, Kwa-Zulu-Natal has the lowest levels of testing at 71% [14]. Of the women tested for HIV, about a third do not receive their test results [3,15]. In 2007, 76*% *of pregnant WLH who did receive their test results received Nevirapine (NVP) during labour, while 57% of infants received NVP at birth [13,16].

Health service coverage for women and children in South Africa is good, as 92% of pregnant women have access to antenatal care [15]. Women generally begin antenatal care prior to the third trimester (54%), and 89% of babies are born in a health facility [15]. While full implementation of all public health innovations takes time [17], South Africa has many components in place to eliminate the vertical transmission of HIV.

However, prevention of HIV transmission and the continued well-being of the mother, child and family involve much more than HIV testing and ARV regimes. Receiving an HIV diagnosis during pregnancy often elicits feelings of anxiety, depression and social isolation [18-20]. Poor mental health and a lack of social support are, in turn, associated with decreased uptake of ARV, decreased adherence to ARV medication, and faster disease progression [21,22]. In addition to decreased social support and mental health, WLH face numerous challenges throughout the perinatal period. Women's antenatal clinic records do not follow them to the delivery centre, requiring the disclosure of HIV status to nurses in order to receive ARV medication.

Similar challenges occur at the post-birth medical appointment and the six week follow-up for infant HIV testing. Results of the baby's HIV status often take weeks or months to be available, requiring multiple maternal visits to the well-baby clinic. Co-trimoxazole is administered to 8% of infants under two months of age who are exposed to maternal HIV, but where status is not identified [23]. In addition to health concerns, a WLH must decide whether, when, and to whom she will disclose her HIV status. In particular, she must decide whether to disclose to her sexual partner, and how to encourage him to be tested for HIV.

In addition to HIV, WLH face intersecting epidemics of alcohol and malnutrition. South Africa has the highest documented rate of Fetal Alcohol Syndrome (FAS) globally [24], and the rate has been increasing [25]. Although health services should address alcohol and nutrition problems, South African antenatal programmes do not include standard screening or counselling of pregnant women regarding alcohol use. Even though vitamin supplements and folic acid are provided to enhance nutrition through antenatal care, 17% of babies are less than 2500 grams, 24% are stunted and/or malnourished under the age of 5 years old, resulting in lifelong negative health outcomes [26]. Co-morbid alcohol use and depression negatively impact infant birth weights [27] and in South African townships, post-partum depression rates exceed 30% [28]. Even low levels of maternal alcohol consumption are related to negative developmental sequelae [29]. Most South Africans consider more than one antenatal care visit unnecessary [30], therefore WLH are unlikely to receive the information, skills, and support needed to consistently maintain healthy routines for themselves or for their child.

The current project examines the effectiveness of paraprofessional community health workers, *Peer Mentors *(PM) to help WLH in the intervention to cope with a range of health and mental health challenges. Peer Mentors are WLH who have been through PMTCT and are themselves thriving, based on the theory of positive peer deviants [31]. Training of the Peer Mentors focuses on existing evidence-based HIV, child health, mental health and alcohol-related interventions [9,32-34]. *The Masihambisane Project*, which means "we walk together" in Zulu, was initiated to test the effectiveness of a Peer Mentor programme in improving the health and well-being of WLH and their babies in PMTCT services provided by the public sector [35] in a very high seroprevalence area.

## Methods/Design

### Objectives

*Masihambisane *is a cluster RCT to test the effectiveness of Peer Mentor support in addressing health, mental health, and stigma challenges faced by WLH. The challenges of chronic illnesses, mental health symptoms, infant feeding and treatment are confronted by WLH on a consistent, daily basis, therefore no single outcome can definitively validate the effectiveness of this Peer Mentor program. We focus on cumulative change across 15 indicators of maternal and infant health. The health-protective behaviors of WLH are documented over time and compared to the baseline rates. These indicators range in their uptake, for example, 92% of babies receive their vaccinations on time, however, infant HIV testing and receipt of results occurs less frequently.

We hypothesize that WLH and their infants in the intervention clinics, compared to WLH who receive standard PMTCT care, will have:

- higher maternal knowledge about HIV self-management;

- better maternal ARV adherence antenatally and at the time of birth;

- increased HIV testing of their baby at six weeks and receipt of test results;

- adherence to regular health visits and TB testing;

- infant weight of more than 2500 grams at birth with normal growth and development for 12 months;

- greater mental health, social support, and ability to cope with HIV stigma;

- higher rates of HIV testing among sexual partners; and

- higher rates of condom use with partners of serodiscordant HIV status.

In order to achieve statistical significance in the analyses, we need to recruit 1200 pregnant WLH (150 per clinic at 8 clinics) with 600 in the intervention and 600 in the standard-of-care control clinics. Enrollment criteria are: 18 years or older at the time of first assessment, less than 34 weeks pregnant at intake, HIV seropositive, and enrolled in the PMTCT programme at one of the eight study clinics. In addition, prospective participants are asked to indicate their intention to reside in the area for the duration of the study, and they must be able to give informed consent, as judged by the interviewer.

### Design

Eight rural clinics in Kwa-Zulu-Natal were matched on information collected from clinic surveys and observations regarding client load, patient characteristics, range of services offered, and rural-urban setting. The UCLA team, without first-hand experience of the clinics, then randomized clinics to the intervention or the standard care condition.

Standard care includes: dual therapy for PMTCT, referral to Highly Active Anti-Retroviral Therapy (HAART) for women with CD4 counts below 200 or WHO Stage 4 illness, infant PCR test results by six weeks of age, and co-trimoxazole for exposed infants starting at six weeks of age [36]. The intervention clinics will receive the standard care in addition to Peer Mentor support sessions. Peer Mentors were selected from the local communities, based on their HIV seropositive status and role as positive peer deviants. Peer Mentors were trained to deliver four antenatal and four postnatal small group sessions in the clinics to supplement the PMTCT program. An independent assessment team conducted in-person interviews with WLH during pregnancy, and within six weeks, six months and twelve months post-birth, evaluating each WLH and her baby's health and well-being.

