### Research activities and procedures

#### Pilot activities

*1. Clinic selection and matching criteria*. Geographic maps, administrative data from the health district, and a month-long observational period in each clinic provided information necessary for selection of clinics for study inclusion. Clinics were identified on the following criteria: a) location - rural (n = 4) or urban (n = 4); b) clinic type - community (n = 2) or primary health care centre (n = 6); c) size of catchment area; d) monthly census of pregnant women; and e) resources such as space, staffing, and transport.

*2. Piloting of the assessment and the intervention*. All instruments and intervention sessions were piloted through focus groups and key informant interviews. These pilot activities involved officials from the KZN Department of Health, including Cluster Heads, District Managers, Medical Managers and Programme or Clinic Managers, Department of Health Clinic Service Providers, and clinic staff members. WLH also participated in pilot sessions of the planned intervention.

*3. Programming and bench testing of mobile phones for collection of assessment interviews*. Data is collected on mobile phones running a survey software package (Mobile Researcher; http://www.populi.net/mobileresearcher/). This platform allows the phone to be used to collect and upload numeric, voice and text data. Two models of phones were used in the pilot - the Nokia E61i (a business phone similar to a PDA) and the Nokia 2630 (an inexpensive candybar phone). Initial training covered practical aspects of phone navigation, checking for software updates, use of the software, and uploading data to the central server. Staff spent two weeks familiarising themselves with the baseline survey on the phone. During this time multiple tests were run to ensure that all data entered on the phone was correctly uploaded and that the response entered on the mobile corresponded to the value stored in the database.

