### Data Collection

Four types of data are consistently monitored:

*1. Clinic data to ensure matching of intervention and standard care clinics. Masihambisane *staff collect aggregated clinic level data for all study clinics: total patients, women attending antenatal care, HIV tests, results received, and participants enrolled in the study. This allows monitoring of enrollment, attrition, and those receiving PMTCT. Figure 2 shows the flow of participants through the data collection process from entry at the clinic, through the consent process, session attendance and post birth assessment.

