**includes the Edinburgh Postnatal Depression Scale [40] and the General Health Questionnaire. 5) **
*Social support *
**includes an adapted scale from Barrera [41] assessing instrumental, emotional, and childrearing support as well as family, neighbour, and community support for healthy acts. The indices are monitored throughout the intervention and at the final assessment.

Intervention effectiveness is assessed by comparing the composite outcome over 12 months between the intervention and standard-of-care control conditions. These composite scores will be compared using multilevel models, i.e., hierarchical models and random effect models, which account for clustering of repeated assessments within individuals and clustering of individuals within clinics [42]. Multilevel models can be applied to normally distributed and non-normally distributed outcomes, we will choose the most appropriate model based on the data. If data transformations sufficiently normalize the composite outcome, e.g., a logarithmic transformation to reduce skewness, we will fit a linear model. If a normal assumption is not appropriate, we will categorize the data and use a longitudinal logistic regression for binary responses [43] and longitudinal ordinal logistic regression to look for shifts in ordinal response levels between the intervention conditions [44]. In all analyses, clustering within clinic will be taken into account, and multiple imputation methods will be used for missing individual outcome scores [45,46].

While the primary outcome composite score will provide a summary of the overall effectiveness of the intervention program, we will also examine each outcome component for a more detailed interpretation. This will be done using longitudinal logistic regression for binary data, to determine whether, and in what direction, the intervention is associated with changes in each component.

Finally, dose-response analysis will be conducted to test for relationships between the number of intervention sessions attended, as well as time of recruitment, and the composite score. The initial patterns of the outcome measures will be examined through descriptive summaries. If necessary, transformations will be conducted to approximate normality, homogeneous variance and linearity in the model.

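### The protocol gives two different rural-urban counts for its eight clinics, and its primary model states no term for the matching and no role for baseline data

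*Protocol article*

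**What the plan says.** Clinic setting is described in two places.

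- Design: "Eight rural clinics in Kwa-Zulu-Natal were matched on information collected from clinic surveys and observations regarding client load, patient characteristics", and the list continues with "range of services offered, and rural-urban setting". The study team "then randomized clinics to the intervention or the standard care condition". Neither the unit of matching (pairs or larger sets) nor whether allocation was made within matched sets is given.
- Pilot activities, item 1 (clinic selection and matching criteria): "location - rural (n = 4) or urban (n = 4"). The same list gives clinic type as two community and six primary health care centres.

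Matching is mentioned again in Data Collection, where one data stream is described as "Clinic data to ensure matching of intervention and standard care clinics".

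In Data Analysis, the composite is compared between arms by multilevel modelling. Two sources of correlation are named for it: "which account for clustering of repeated assessments within individuals and clustering of individuals within clinics". A later sentence in the same section adds: "In all analyses, clustering within clinic will be taken into account". No matched set, stratum, matching variable or baseline covariate is named.

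On baseline, Objectives says that behaviours are compared with baseline rates, Recruitment describes a baseline interview after consent, and Data Collection lists CD4 count among the items taken from medical records. Data Analysis lists only the post-birth assessments.

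**The concern.** A factor that takes one value in all eight clinics cannot be matched on, so the Design sentence conflicts with itself as well as with Pilot activities. The error is in a design fact, so no analysis plan can settle it. A reader cannot tell whether the result applies to rural clinics or to a mixed set, or whether setting is available as a design factor.

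The second part concerns the model. With four clinics per arm, chance differences between clinics are likely and between-clinic variance dominates the standard error. Matching and baseline data are the two means this trial has of limiting that. The description of the primary model is fairly full on levels, distributions, transformations and imputation, yet it assigns neither of them a place.

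**Working it through.** **1. The passages side by side.** Design gives 8 rural and 0 urban; Pilot activities gives 4 rural and 4 urban. The totals agree (8) and the split does not.

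**2. The plan's own figure.** Objectives gives 150 women per clinic at 8 clinics: 150 × 8 = 1200, and 150 × 4 = 600 per arm. Both agree with the text. The article gives no ICC, standard deviation, effect size or power, so what follows assumes two-sided alpha 0.05, 80% power and ICC 0.01 to 0.05.

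**3. How much of a clinic mean's variance lies between clinics.** With total variance 1 and m = 150, share = ICC / [ICC + (1 − ICC)/m].

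| ICC | (1 − ICC)/150 | Share |
|---|---|---|
| 0.01 | 0.0066 | 0.60 |
| 0.02 | 0.0065 | 0.75 |
| 0.05 | 0.0063 | 0.89 |

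**4. Break-even for a design-factor term.** The detectable difference is approximately (t₀.₉₇₅ + t₀.₈) × SE. Eight clinics in two arms leave 6 df; one stratum term leaves 5; four pairs leave 3.

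- 6 df: 2.447 + 0.906 = 3.353
- 5 df: 2.571 + 0.920 = 3.490
- 3 df: 3.182 + 0.978 = 4.161

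The share of clinic-mean variance that must be explained to break even is:

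- one stratum term: 1 − (3.353/3.490)² = 0.077
- four pairs: 1 − (3.353/4.161)² = 0.351

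These are shares of the whole clinic-mean variance, which includes sampling error within clinics. Dividing by the shares in step 3 converts them to shares of between-clinic variance:

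| ICC | One stratum term | Four pairs |
|---|---|---|
| 0.01 | 0.077/0.60 = 13% | 0.351/0.60 = 58% |
| 0.02 | 0.077/0.75 = 10% | 0.351/0.75 = 47% |
| 0.05 | 0.077/0.89 = 9% | 0.351/0.89 = 40% |

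As a check with the noncentral t at ICC 0.02, the detectable difference is 0.388 SD with no design term. With one stratum term it is 0.405, 0.356 or 0.319 SD if the term removes 0, 30 or 50% of between-clinic variance. With four pairs it is 0.490, 0.431 or 0.387 SD for the same percentages, so pairs only draw level at about 50%.

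**5. Baseline covariates.** Assume a within-clinic correlation of 0.4 with the outcome and a clinic-level correlation r_c. The fall in variance of the arm difference is r_c² × share + 0.16 × (1 − share).

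| Clinic-level correlation | ICC 0.01 | ICC 0.05 |
|---|---|---|
| 0 | 0.16 × 0.398 = 6% | 0.16 × 0.112 = 2% |
| 0.4 | 16% | 16% |
| 0.6 | 0.36 × 0.602 + 0.16 × 0.398 = 28% | 0.36 × 0.888 + 0.16 × 0.112 = 34% |

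At unchanged df the detectable difference scales with the square root of the remaining variance. It falls by 1-3% in the first row (√0.98 to √0.94) and by 8-19% across the other two (√0.84 to √0.66). If the covariates also cost one clinic-level df, these ratios are multiplied by 3.490/3.353 = 1.041. The 8-19% becomes 5-15%, and the first row turns into a loss of about 1-3%.

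**The case against.** The strongest reply is that this is a journal article. It describes a family of models and says the choice will depend on the data, and the covariate list and the handling of matched sets can reasonably sit in a fuller plan. That is fair. A reader might infer from the Data Analysis text that the matching and the baseline data are deliberately discarded. The document does not support that: nowhere does it exclude them, Objectives promises a comparison with baseline, and the pregnancy assessment could be one of the repeated assessments in the model. What stands is that their role is unstated.

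A reader might also infer that clinics were randomised within matched pairs and that an analysis without pairs is therefore wrong. The article says only that clinics were matched and then randomised. Even with pairs, ignoring them is a recognised choice with eight clusters, because it keeps 6 df rather than 3.

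It can also be said that the composite has no full baseline value, since birth weight, infant nevirapine, baby testing and feeding method have no antenatal counterpart. That is correct, and it rules out adjusting for a baseline composite. It does not rule out other entry characteristics as covariates.

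Finally, the gain from covariates rests on assumed correlations. Nothing in the document shows that age, gestational age or CD4 count predicts a largely behavioural and psychosocial composite. That objection stands in full, and the low end of the range must be taken seriously.

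None of these replies touches the rural-urban contradiction.

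**Conclusion.** The contradiction is certain from the text: eight rural clinics matched on rural-urban setting cannot be reconciled with four rural and four urban. The passages must be made to agree.

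The modelling part holds as an improvement worth making, with moderate confidence. The stated primary model has no term for the matching and does not place the baseline data that the protocol promises and collects. Leaving them out costs precision and protection against chance imbalance. It does not make the analysis invalid, and no bias is shown.

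The size is conditional. A single stratum term has a low threshold, about 8% of clinic-mean variance, and a small loss if it explains nothing (0.388 to 0.405 SD at ICC 0.02). Four pair effects have a high threshold and are not recommended. Baseline covariates may bring little (2-6% of variance) or a useful amount (16-34%), depending on clinic-level correlations that the document does not give.

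**What to change.** 1. Correct Design or Pilot activities, whichever is wrong, so that both give the same rural-urban count.
2. State the unit of matching and whether clinics were randomised within matched sets.
3. In the primary model, add individual baseline covariates that are already collected and that Peer Mentor contact cannot alter: age, gestational age at entry and CD4 count. This restriction matters because Recruitment allows women in intervention clinics to meet a Peer Mentor before consent and the baseline interview. Parity is not named among the collected items, so it should not be relied on.
4. If clinics were matched or randomised within rural-urban setting, add it as one fixed effect. If all clinics prove to be rural, use clinic type on the same condition. Do not fit four pair effects.
5. Say in Data Analysis how the baseline comparison promised in Objectives is made.

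The cost is a corrected sentence, a few lines of model specification, and one clinic-level degree of freedom (6 to 5) for the stratum term. No new data are needed.
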